### Primary outcome measures

#### Knee injury and osteoarthritis outcome score (KOOS)

The Knee Injury and Osteoarthritis Outcome Score (KOOS) is a self report questionnaire with 42-items in 5 separately analyzed subscales of pain, other symptoms, function in daily living, function in sport and recreation, and knee–related quality of life [31]. The tool has good test-retest reliability with ICC _(2,1)_ values in 26 patients 6 months post TKA of 0.73 (QOL), 0.74 (Sport/recreation), 0.82 (ADL), 0.85 (Symptoms), and 0.94 (Pain). Good content validity demonstrated by 90 % of patients who regarded improvement in the subscales Pain, Symptoms, Activities of Daily Living, and knee-related Quality of Life to be extremely or very important when deciding to have their knee operated on. The KOOS is responsive on all subscales particularly the knee-related Quality of Life subscale (effect size 2.86 at 6 months post TKA and 3.54 at 12 months post TKA) [32].

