#### Data and statistical analysis

An estimate of sample size was made on the ability to detect a medium effect (Cohen’s f = 0.25). The assumption of obtaining a medium effect size was reasonable based on the effect sizes reported for similar measures such as the WOMAC by other studies in the literature (effect size for WOMAC function = 0.3, WOMAC pain = 0.31) [18]. A standard statistical package was used [78]. To obtain a power of 0.8 at a significance level of α = 0.05, a minimum sample of 82 participants would be needed. To allow for loss to follow-up the aim was to recruit a sample of approximately 104 participants.

Participant characteristics and baseline data will be summarized by descriptive statistics. Independent sample t-tests for parametric data (or a chi-squared test for categorical data) will be used to determine the comparability of the two groups at baseline on measures of age, gender and BMI. All data will be analysed using intention to treat principles. Any missing data will be replaced by the last observation carried forward. Repeated measures ANOVA (group by time) calculations will be used to determine the main effects and interactions of group (hip abductor strengthening vs usual care exercises) and time (repeated factor: baseline, 3 weeks, 6 weeks, 6 months) for all outcome measures. Statistical analysis will be completed using SPSS software (version 22) and the significance level set at *P <* 0.05.

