It is important to evaluate the effectiveness of rehabilitation programs with appropriate outcome measures. This trial has ensured that outcome measures are included from the three different domains of physical impairment, patient reported measures, and physical performance measures, as recommended by OARSI and Mizner et al. [29, 36]. This is advantageous because many of the outcome measures for the different domains improve at different rates post-operatively. In the early stages after TKA surgery scores on the patient reported outcome scales are significantly better than preoperative scores, while functional performance outcome measures are reduced [36]. This may be due to the experience of pain free movement combined with the ability to perform a previously painful and difficult activity again resulting in high patient satisfaction and is reflected in the high scores of patient reported outcome scales [85]. The performance-based tests demonstrate an initial reduction in physical function in patients following TKA that is not seen in patient-reported measures [36]. From 1 month to 6 months postoperatively, patients’ physical performance improves [3, 43, 83] with the highest rate of improvement occurring in the period from 1 to 3 months compared with the period from 3 to 6 months [43, 35]. The outcome measures included in this trial ensure an accurate picture of recovery will be recorded.

In the evaluation of the effects of hip strengthening following TKA, it is important to determine that hip strengthening has occurred as a result of the intervention. The method of strength measurement may be considered a limitation of the study however the use of a hand-held dynamometer rather than a mechanical isokinetic dynamometer is reliable and valid with a seatbelt for restraint [33]. As this study will be conducted during the participants’ rehabilitation in a small hospital, access to an isokinetic dynamometer is not possible.

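### Carrying the last observation forward while patients are still recovering can bias the 6-month and group-by-time results in either direction

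*Protocol article*

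**What the plan says.** Under Data and statistical analysis the protocol article fixes one rule for every gap in the data: "Any missing data will be replaced by the last observation carried forward". It applies within an intention-to-treat analysis ("All data will be analysed using intention to treat principles") by repeated measures ANOVA of group by time, with "time (repeated factor: baseline, 3 weeks, 6 weeks, 6 months) for all outcome measures".

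Loss is expected. The sample size is stated as "To obtain a power of 0.8 at a significance level of α = 0.05, a minimum sample of 82 participants would be needed", followed by "To allow for loss to follow-up the aim was to recruit a sample of approximately 104 participants".

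On the course of recovery, the Discussion says that physical performance improves between 1 and 6 months after surgery, "with the highest rate of improvement occurring in the period from 1 to 3 months compared with the period from 3 to 6 months". Under Outcome measures, baseline is placed about 7 days after surgery and the later visits at 3 weeks, 6 weeks and 6 months from the start of rehabilitation.

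**The concern.** Carrying the last value forward gives a fair 6-month score only if the participant would not have changed after leaving. The protocol's account of physical performance says otherwise. Six weeks after a day-7 baseline is about 7 weeks after surgery. That is inside the 1-to-3-month window of fastest improvement, and nothing is measured between then and 6 months. Someone lost after baseline, week 3 or week 6 is analysed at 6 months as if recovery had stopped there.

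Two things are at stake. If the arms differ in how many participants they lose, or when, the arm with more or earlier loss tends to look worse. The trial could then miss a benefit or report one that does not exist. If loss is equal, mixing frozen early scores with true 6-month scores widens the spread within each arm, and it can dilute a treatment effect that is still growing. In both cases the filled-in values are counted as real observations.

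**Working it through.** **1. The plan's own figure.** Inputs from the document: f = 0.25 (for two groups d = 2f = 0.5), power 0.8, α = 0.05, two groups, four measurements. The correlation between visits is not given; 0.5 is assumed. For the between-groups effect, λ = N f² m / (1 + (m − 1)ρ) = 82 × 0.0625 × 4 / 2.5 = 8.2, which gives power 0.808. The 82 reproduces. The allowance is (104 − 82)/104 = 21.2% loss.

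**2. Evidence of later gain in the document.** Stair climb: effect size 1.26 from 1 to 12 months. Six-minute walk: 0.82 from two to four months. Both come from cited cohorts, over intervals that do not match this trial's visits.

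**3. Assumptions for the illustration.**
- 52 per arm, SD 1 at each visit, loss unrelated to outcome.
- Mean recovery at baseline, 3 weeks, 6 weeks and 6 months: profile A (0, 0.5, 0.8, 1.2) SD; profile B (0, 0.8, 1.4, 2.0) SD.
- Timing of loss: either all after week 6, or one third after each of the first three visits.

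The correlation does not enter the 6-month calculations below, because a carried-forward score has SD 1 whatever the correlation.

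**4. Unequal loss, no true effect.** False difference = (difference in proportion lost) × (mean gain missed).
- Gain missed, late loss: A 1.2 − 0.8 = 0.4; B 2.0 − 1.4 = 0.6.
- Gain missed, even loss: A (1.2 + 0.7 + 0.4)/3 = 0.767; B (2.0 + 1.2 + 0.6)/3 = 1.267.
- Loss of 16% v 26%, late: 0.10 × 0.4 = 0.04 and 0.10 × 0.6 = 0.06 SD.
- Loss of 16% v 26%, even: 0.10 × 0.767 = 0.08 and 0.10 × 1.267 = 0.13 SD.

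Timing alone can do the same. With 21% lost in both arms, late in one and evenly in the other, the false difference is 0.21 × (0.767 − 0.4) = 0.08 SD (A) or 0.21 × (1.267 − 0.6) = 0.14 SD (B).

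A stress case shows the effect on the planned tests. Take 22 losses split 16 v 6, no true effect, and means of 0, 0.6, 1.0 and 2.0 SD. In simulation at a nominal 5%, the 6-month test rejected 13 to 20% of the time, the group-by-time interaction 12 to 19%, and the group main effect 6 to 10%.

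**5. Equal 21% loss, growing effect (0, 0.25, 0.4, 0.5).** Variance per arm = 1 + E(g²) − E(g)², where g is the gain missed (zero for completers).

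| Timing | Raw difference | SD, A / B | Standardised d, A / B | Power, 52 per arm, A / B |
|---|---|---|---|---|
| Late | 0.79 × 0.5 + 0.21 × 0.4 = 0.479 | 1.017 / 1.035 | 0.47 / 0.46 | 66% / 65% |
| Even | 0.79 × 0.5 + 0.07 × (0 + 0.25 + 0.4) = 0.4405 | 1.085 / 1.193 | 0.41 / 0.37 | 54% / 46% |

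Power is for a two-group test at 6 months. The fair comparator is 82 completers (41 per arm) at d = 0.5, which gives 61%.

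**6. Benchmark without carry-forward.** With loss at random, a simulated 6-month comparison on observed values alone gave 0.49 to 0.51 SD for a true 0.50. Its type I error was 0.04 to 0.06, whichever arm lost more. The mixed model itself was not simulated.

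**The case against.** Several points on the other side stand, and they set the size of this finding.

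- **The primary outcomes.** The documented 1-to-6-month recovery concerns physical performance, which is secondary. The article describes patient-reported scores as improving early. It also says that hip abductor weakness persists under current rehabilitation. A reader might take the KOOS quality-of-life figure, "effect size 2.86 at 6 months post TKA and 3.54 at 12 months post TKA", as the gain from this trial's baseline. The article states no reference point for it and does not tie it to day 7, so it is not used here.
- **Bias whenever loss differs.** A reader might infer this, but it is not universal: the bias vanishes if proportion lost × gain missed is equal in the two arms.
- **Shrinkage under any equal loss.** This is not universal either. With a fading effect (0.75 at the last visit, 0.50 at 6 months) and 11 lost per arm, the standardised effect is 0.53 at a missed gain of 0.82 and 0.50 at 1.26.
- **Power.** A reader might set these figures against the 71% available with 104 complete participants. That ignores the planned loss. Against 61%, carrying forward costs no power when loss is late.
- **Differential loss.** Nothing in the article predicts it. The arms are matched for session time, and participants are not told their group. The 16% v 26% split is an assumption.
- **The planned test.** No 6-month primary comparison is named, and the group main effect is less exposed than the interaction.

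An analysis plan not shown could add sensitivity analyses, but the protocol has already committed to the main rule. None of this supplies a reason to expect flat scores after dropout in the performance outcomes.

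**Conclusion.** The concern holds in a limited form. The rule conflicts with the protocol's own description of performance recovery, and it can distort the 6-month contrast and the group-by-time interaction. The direction depends on which arm loses more or earlier, so the rule cannot be defended as conservative.

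Under the stated assumptions the false difference is modest: 0.04 to 0.13 SD at 16% v 26%, against a planned d of 0.5. Heavier imbalance makes it larger. With equal loss and a growing effect, the standardised effect falls to 0.46 to 0.47 (late loss) or 0.37 to 0.41 (even loss). Only the even-loss case puts power below that of 82 completers.

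These sizes rest on assumed recovery profiles, visit SDs, loss rates and timing, none of which the article gives. The case is clearest for the performance outcomes and not quantified for KOOS or hip abductor strength. This should be fixed; it does not invalidate the design.

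**What to change.** Delete the carry-forward sentence. Analyse all observed data from all randomised participants with a likelihood-based mixed model for repeated measures: visit as a category, group-by-visit interaction, and baseline accounted for. This is valid if data are missing at random. Add one sensitivity analysis for departures from that assumption, and report the amount and timing of loss by arm. Settle the wording before any unblinded look at the outcomes.

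The cost is a change of wording and a little extra analysis. The MIXED procedure in SPSS, the package already named, fits the model. No new data, visits or participants are needed, and the targets of 82 and 104 can stay.

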### Randomisation and allocation concealment

Eligible patients will be identified by the treating physiotherapist. The treating physiotherapist will inform the patient of the study, give them the patient information sheet and arrange for a meeting with the primary researcher. The primary researcher will discuss any questions with the patient and gain informed consent of willing participants. Eligible patients will be randomized by a computer-generated list of random numbers to usual care or usual care plus hip strengthening. An independent person, not involved in delivering the intervention or testing, will manage the allocation list and numbered opaque envelopes containing the allocated group of each participant. Only the treating physiotherapist will be informed of the group allocation of the participants. The allocation list will not be available to the researchers and the participants will not be informed which group they are in. The participants will be informed that there are two different rehabilitation programs but will not be told that one program is specifically targeting hip strengthening exercises. This is to prevent potential bias from knowledge of treatment. The rehabilitation will be conducted in a large busy gym where there are many different patients with different diagnoses treated at the same time by their individual physiotherapists with individual exercise programs dependent on each patient’s needs. This will reduce the probability of patients from one intervention seeing the other intervention group’s exercises. A survey on exit from the study will be conducted to determine which group the participants thought they were in during their rehabilitation.

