Primary and secondary outcomes will be measured at admission to inpatient rehabilitation (approximately 7 days post-operatively), 3 weeks, 6 weeks and 6 months after commencing the rehabilitation program. A discrepancy is often reported in the recovery of patient reported outcomes compared to functional performances, with the more rapid improvement noted in patient reported outcome scales while functional performance measures are often significantly reduced in the early post-operative period [30]. Therefore, the two types of outcome measures have been included to ensure an accurate representation of rehabilitation outcomes following TKA.

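### Baseline enters the repeated-measures ANOVA as a fourth outcome level and not as a covariate, so the group main effect understates a treatment difference and the interaction does not estimate one

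*Protocol article*

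**What the plan says.** Under Data and statistical analysis, the protocol article states the model: "Repeated measures ANOVA (group by time) calculations will be used to determine the main effects and interactions of group" and of "time (repeated factor: baseline, 3 weeks, 6 weeks, 6 months) for all outcome measures". Under Outcome measures it places the first of these visits at the start of the programme: "Primary and secondary outcomes will be measured at admission to inpatient rehabilitation (approximately 7 days post-operatively), 3 weeks, 6 weeks and 6 months" after rehabilitation begins. Allocation is random (Randomisation and allocation concealment): "Eligible patients will be randomized by a computer-generated list of random numbers to usual care or usual care plus hip strengthening".

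The sample size paragraph is brief: "An estimate of sample size was made on the ability to detect a medium effect (Cohen’s f = 0.25"), then "To obtain a power of 0.8 at a significance level of α = 0.05, a minimum sample of 82 participants would be needed", and "To allow for loss to follow-up the aim was to recruit a sample of approximately 104 participants". It does not state the number of measurements, the within-person correlation, or which ANOVA effect was powered.

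Apart from its place in the time factor, baseline is used only to describe the sample and to compare the groups on age, gender and BMI. The article does not say whether the main effect or the interaction decides the trial.

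**The concern.** The trial asks whether added hip strengthening gives better strength, patient-reported and performance outcomes than usual care. That calls for a between-group difference after treatment, with a sign and a size. The stated model offers two tests, and neither supplies it directly.

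- The group main effect averages over all four visits. At one of them treatment has not yet acted, so the average is pulled towards zero.
- The group-by-time interaction asks whether the two recovery profiles differ in shape anywhere. A significant result does not show which group is better, when, or by how much.

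At stake are a diluted estimate if the main effect is reported as the treatment effect, and a power statement that may belong to that diluted test. Every baseline value that would sharpen the comparison is already being collected.

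**Working it through.** **Inputs from the article:** f = 0.25, alpha = 0.05, power 0.80, N = 82, recruitment target 104, four visits with baseline first.

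**Assumptions:** equal allocation (ratio not stated); d = 2f = 0.5 SD at each follow-up and 0 at baseline; equal variances; the same correlation r between any two visits (not stated; r = 0.5, with 0.3 and 0.7 shown). Power is from the non-central F distribution with noncentrality λ.

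**Step 1. Reproduce the stated 82.** For the group main effect over m visits, λ = f²·N·m / [1 + (m − 1)r], with 1 and N − 2 df. With m = 4 and r = 0.5:

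λ = 0.0625 × 82 × 4 / 2.5 = 8.2, power 0.808. N = 80 gives 0.798, so 82 is the smallest even total that reaches 0.80.

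At r = 0.5, three visits would need 86, a single visit 128, and the four-visit interaction 24. Of these variants, only the four-visit main effect gives 82. That formula credits the full effect to every visit, baseline included.

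**Step 2. Set the baseline effect to zero.** The main effect then estimates (0 + d + d + d)/4 = 0.75d = 0.375 SD. The factor 0.75 does not depend on r or N. The variance of a four-visit mean is (1 + 3r)/4 = 0.625, so

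λ = (82/4) × 0.375² / 0.625 = 4.61, power 0.56.

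About 142 participants would be needed for 0.80. If all 104 are analysed, power is 0.67.

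**Step 3. The interaction.** The deviations of (0, d, d, d) from their mean have sum of squares 0.375² + 3 × 0.125² = 0.1875. Then λ = (N/4) × 0.1875 / (1 − r) = 20.5 × 0.1875 / 0.5 = 7.69, with 3 and 3(N − 2) = 240 df; power 0.63.

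**Step 4. Baseline-adjusted contrasts** (1 and N − 3 = 79 df).

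- Mean of the three follow-ups: residual variance (1 + 2r)/3 − r² = 0.667 − 0.25 = 0.417. λ = 20.5 × 0.25 / 0.417 = 12.3, power 0.93.
- 6-month value alone: residual variance 1 − r² = 0.75. λ = 20.5 × 0.25 / 0.75 = 6.83, power 0.73.

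**Step 5. Range over r** (N = 82, constant d = 0.5):

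| r | Main effect, 4 visits | Interaction, 3 df | Adjusted follow-up mean | Adjusted 6-month value |
|---|---|---|---|---|
| 0.3 | 0.68 | 0.47 | 0.92 | 0.65 |
| 0.5 | 0.56 | 0.63 | 0.93 | 0.73 |
| 0.7 | 0.48 | 0.86 | 0.98 | 0.88 |

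**Step 6. Other effect shapes** (r = 0.5, N = 82):

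| Effect at 0, 3 weeks, 6 weeks, 6 months (SD) | Main effect | Interaction | Adjusted follow-up mean | Adjusted 6-month value |
|---|---|---|---|---|
| Rising: 0, 0.17, 0.33, 0.5 | 0.29 | 0.49 | 0.64 | 0.73 |
| Fading: 0, 0.5, 0.5, 0 | 0.29 | 0.77 | 0.64 | no effect to detect |

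**The case against.** The strongest reply is that group-by-time ANOVA with baseline as a level is conventional and valid. The interaction tests differential change from baseline, which suits the stated purpose of the visit schedule (tracking the rate of improvement, Trial design), and the article never says that the main effect decides. All of this stands. At r = 0.7 the interaction has power 0.86 under a constant effect. If the effect is present at 3 and 6 weeks but gone by 6 months, it beats the adjusted follow-up mean, 0.77 against 0.64. That shape is possible, because supervised sessions stop well before the last visit and only home exercise continues.

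The size of the gain also depends on the comparator. Against an adjusted 6-month contrast, the better of the two planned tests is about level at r = 0.3 (0.68 against 0.65) and r = 0.7 (0.86 against 0.88), and ten points lower at r = 0.5 (0.63 against 0.73).

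A reader might infer three stronger things that the article does not support:

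- That the plan throws away most of the available power. Even against the most favourable comparator, the better planned test keeps 0.68 of 0.92, 0.63 of 0.93 and 0.86 of 0.98.
- That unequal visit spacing inflates the type I error of the interaction. This would need an F test without a sphericity correction. The article does not say that the test is uncorrected, and such a correction is normally left to an analysis plan.
- That the main effect is biased as such. It correctly estimates a four-visit average and is valid under the null. It misleads only if read as the post-treatment difference.

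Follow-up contrasts may also be set out in an analysis plan that is not shown. The point therefore rests on the model and factor levels that the article does state.

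**Conclusion.** The point holds in a limited form. The stated model makes the pre-treatment visit an outcome level and does not adjust for the baseline outcome. If the group main effect is taken as the treatment effect, it recovers 75% of a constant post-treatment difference. That figure needs only randomisation and a constant effect. The fall in power from 0.80 to 0.56 at N = 82 also assumes d = 0.5 and compound symmetry with r = 0.5. That 82 was derived from this main effect is an inference from an exact match, since neither the correlation nor the procedure is given.

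The interaction is a sound test of whether the profiles differ, but it does not answer the trial's directional question. Baseline adjustment supplies an estimate that does. It usually gains power too, by an amount that varies with the correlation, the contrast and the shape of the effect.

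**What to change.** Replace the four-level ANOVA with a linear mixed model for the 3-week, 6-week and 6-month values. Include the baseline value of the same outcome as a covariate, and fixed effects for group, visit and group-by-visit. A constrained longitudinal model with a common baseline mean is an equivalent choice. Report the adjusted group difference with its 95% CI at each visit.

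Name in advance the one contrast from which the conclusion is drawn, such as the follow-up mean or the 6-month difference, and choose it for the effect pattern that matters clinically. Then recheck the stated power for that contrast, giving the assumed correlation. If a fading effect is thought likely, an early-visit contrast or the interaction as a supporting test can be kept.

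The cost is a paragraph of analysis text and a new power calculation. No extra visits or data are needed, and the mixed-model procedure in the named SPSS version can fit the model.

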### Secondary outcome measures

#### Stair climb test

The stair climb test has been used extensively as an outcome measure in TKA [3, 13, 35–37]. The test assesses the time, in seconds, to ascend and descend a flight of stairs. The number of stairs in the flight and the step height are recorded. In the current study, a four-step staircase will be used. The use of a handrail and gait aids are permitted and will be recorded, as will be the footstep pattern (reciprocal or step-to). Inter-rater reliability was reported as ICC _(2,1)_ = 0.94 (95 % CI =0.55-0.98). MDC_90_ was calculated as 2.6 seconds [38]. The stair climb test has demonstrated adequate construct validity [39] and responsiveness detecting initial deterioration (effect size = −0.84) from pre-op to 1 month post-TKA scores, and then subsequent improvement (effect size = 1.26) from 1 month to 12 months post-TKA on a 12-step flight [36].

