#### Timed up and Go Test (TUG)

The timed up and go test (TUG) measures the time, in seconds, that a patient takes to stand from an armed chair, walk for 3 m, and return to sit on the same chair. A walking aid can be used if required [46]. The reliability of the TUG has been established in a study that combined pre-operative TKA and THA subjects. The test-retest reliability was reported as ICC _(2,1)_ =0.75 (95 % CI = 0.51-0.98) [38]. The TUG was found to be selective in its ability to distinguish healthy subjects from TKA patients [47]. It is responsive to detecting early deterioration and improvement in the early post-operative period with standardized response means (SRM) varying from −1.08 (95 % CI −1.38 to −0.92), indicating a worsening in the value to 1.04 (95 % CI 0.84 to 1.61) indicating an improvement in time taken to perform the test. Standard error of measurement (SEM) was calculated as 1.07 (95 % CI = 0.86-1.41) and minimal detectable change at the 90 % confidence level (MDC_90_) was 2.49 seconds [38].

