#### 40 m Fast-paced Walk test

The purpose of the 40 m fast-paced walk test is to assess short distance walking ability [29]. The test measures the time, in seconds, taken to walk 40 m as quickly but as safely as possible excluding turns. The total time is expressed as m/s by dividing distance (40 m) by time (seconds). Any gait aids required are recorded [48]. The reliability and validity of the 40 m fast-paced walk test has been tested in a group of combined pre-operative THA and TKA patients, where test-retest reliability was found to be excellent, ICC _(2,1)_ = 0.91 (95 % CI = 0.81-0.97) and responsiveness to initial surgery followed by recovery was evident [38] Standard error of measurement (SEM) was calculated as 1.73 (95 % CI = 1.39-2.29) and minimal detectable change at the 90 % confidence level (MDC_90_) was 4.04 sec [38].

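### Timed Up and Go and stair climb: a four-level ANOVA in seconds, with the day-7 baseline as an outcome level, may lose substantial power if day-7 times are the most variable

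*Protocol article*

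**What the plan says.** Under Data and statistical analysis, the protocol article plans: "Repeated measures ANOVA (group by time) calculations will be used to determine the main effects and interactions of group" and time. The repeated factor has four levels (baseline, 3 weeks, 6 weeks, 6 months), and the same model serves all outcomes. Outcome measures puts the baseline at about 7 days after surgery.

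Both tests are secondary outcomes measured in seconds. For stair climb: "The test assesses the time, in seconds, to ascend and descend a flight of stairs". For Timed Up and Go, the test "measures the time, in seconds, that a patient takes to stand from an armed chair", walk 3 m and sit down again. Only the 40 m walk is rescaled: "The total time is expressed as m/s by dividing distance (40 m) by time (seconds").

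On the course of recovery, Outcome measures says that "functional performance measures are often significantly reduced in the early post-operative period", and the Discussion says that physical performance improves from 1 to 6 months. Neither place gives a mean or SD by visit for either test.

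**The concern.** Completion times cannot fall below a floor, and slow performers spread out, so the spread usually rises with the mean. If day 7 is the slowest visit, it is probably also the most variable on the seconds scale. Randomised treatment cannot have had an effect at that visit. The planned ANOVA nevertheless averages it into the group main effect and uses it in the group-by-time test. A real difference at 3 weeks, 6 weeks or 6 months is then diluted and set against an inflated error.

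The Background names these two tests as the ones correlated with hip abductor strength. A null result caused by the analysis could be misread as evidence that hip strengthening does not help function.

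**Working it through.** **1. The plan's own figure.** The inputs are "An estimate of sample size was made on the ability to detect a medium effect (Cohen’s f = 0.25") and "To obtain a power of 0.8 at a significance level of α = 0.05, a minimum sample of 82 participants would be needed". For the between-group effect in a repeated measures ANOVA with m visits, λ = f²·N·m / (1 + (m−1)ρ), on 1 and N−2 df. With m = 4 and ρ = 0.5 (assumed, since no correlation is stated):

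- N = 82: λ = 0.0625 × 82 × 4 / 2.5 = 8.2, power 0.808.
- N = 80: λ = 8.0, power 0.798.

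So 82 reproduces as a test of the group effect averaged over four visits, day 7 included. The group-by-time variant gives 24 instead. The target of 104 corresponds to about 21% loss: 82 / 0.79 = 103.8.

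**2. How the day-7 spread acts on the group main effect.** Assume 41 per arm, ρ = 0.5, follow-up SD 3 s, day-7 SD k × 3 s, and a true effect of 1.5 s at each follow-up visit and none at day 7.

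- Effect on the four-visit mean: (0 + 3 × 1.5) / 4 = 1.125 s.
- Variance of that mean: 9·[k² + 3 + 2ρ(3k + 3)] / 16, which for ρ = 0.5 is 9·(k² + 3k + 6) / 16.
- Standardised effect d = 1.125 / SD, noncentrality d·√(41/2), two-sided t test on 80 df.

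| k | variance | d | main-effect power | simulated interaction power (Greenhouse-Geisser) |
|---|---|---|---|---|
| 1 | 5.63 | 0.474 | 0.56 | 0.64 |
| 1.5 | 7.17 | 0.420 | 0.47 | 0.43 |
| 2 | 9.00 | 0.375 | 0.39 | 0.28 |
| 3 | 13.50 | 0.306 | 0.28 | 0.13 |
| 5 | 25.88 | 0.221 | 0.17 | 0.08 |

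**3. The same data with day 7 as covariate.** The variance of the three-visit follow-up mean is 9·(1 + 2ρ)/3 = 6. Its squared correlation with day 7 is (0.5 × 3)² / 6 = 0.375, whatever k is. The residual variance is 6 × 0.625 = 3.75, so d = 1.5 / 1.936 = 0.775 and power is 0.93 for every k. Even at k = 1, where nothing is inflated, the planned main effect has 0.56. That gap comes from counting the untreated visit as an outcome.

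**4. Seconds against log seconds.** Simulation with 52 per arm and complete data. All inputs are assumed: median times 25-14-11-9 s or 18-13-11-9 s; log-SD 0.3 or 0.4; correlation 0.6 throughout or 0.7 per visit step; hip arm 8% faster at 3 weeks and 15% faster at 6 weeks and 6 months. With constant log-SD, the day-7 to 6-month SD ratio equals the ratio of medians: 25/9 = 2.8 or 18/9 = 2.0. Ranges over the eight scenarios:

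| test | raw seconds | log seconds |
|---|---|---|
| group-by-time, Greenhouse-Geisser | 12-38% | 47-87% |
| group main effect | 16-39% | 32-55% |
| covariance analysis of follow-up mean, day 7 as covariate | 63-93% | 69-96% |

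The multivariate interaction test, which does not pool variances over visits, reaches only 11-33% in raw seconds, so visit-specific variances alone do not rescue the raw scale. Once day 7 is a covariate, the log scale adds roughly 2-10 points.

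**5. Type I error.** With no effect, the uncorrected interaction test in raw seconds rejects in about 8% of trials in these scenarios. In the set-up of step 2 it rejects in about 7-11% at SD ratios of 2 to 5. With a Greenhouse-Geisser correction it stays near 5% in both.

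**The case against.** **No means or SDs by visit are given.** This stands. A reader might infer that day-7 times will swamp the later visits and hide a real effect, but the documents support only the direction (early slowness, later recovery). With equal SDs there is no swamping, and at a ratio of 1.5 the loss is moderate.

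**The article gives units of measurement and does not rule out a transformation, which an analysis plan may specify.** This stands for the transformation and for the sphericity correction. It does not cover the time factor: the article states that baseline is one of four levels, for all outcomes.

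**The simulation favours the log scale, because it assumes lognormal times and percentage effects.** Partly right. However, with additive effects on normal data the log scale also had more interaction power: 88% against 83% with equal raw SDs, and 78% against 38% with day-7 SD twice the 6-month SD. Loss to follow-up and last observation carried forward were not modelled.

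**The seconds scale is not the main cause.** This is correct. A log transformation within the same four-level ANOVA leaves the main effect at 32-55%.

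**Seconds match the minimal detectable changes quoted for both tests.** This is a fair reason to keep reporting them. The 40 m walk is only a loose precedent, since Table 4 still lists it as a time and its own minimal detectable change is in seconds.

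**Conclusion.** The point holds conditionally. For these two secondary outcomes, the stated four-level ANOVA in seconds is poorly matched to the data if day-7 times are clearly more variable than later ones. That is likely for completion times, but it is an assumption. At an SD ratio of 2 or more the loss of power is large in both the main effect and the interaction.

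Three stronger readings are not supported:

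- The loss is not certain, because the spread by visit is unknown.
- The interaction test does not reject too often in general. The excess (about 8%) arises only without a sphericity correction, and the article does not say whether one will be used.
- A change of scale is not a sufficient remedy. The larger share of the loss comes from the pre-treatment visit being an outcome level, and that share remains with equal SDs.

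The primary outcomes, KOOS and hip abductor strength, are not affected by the change of scale.

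**What to change.** In Data and statistical analysis, state that Timed Up and Go and stair climb are analysed as log seconds over the 3-week, 6-week and 6-month visits, with the day-7 value (also in log seconds) as a covariate, and that the result is back-transformed to a percentage difference between arms. Speed, as already used for the 40 m walk, is an acceptable alternative. Report raw seconds by visit and arm descriptively, so that the quoted minimal detectable changes can still be read. If a repeated measures ANOVA with a time interaction is kept, name the sphericity correction.

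The cost is a sentence or two in the analysis section and an effect reported as a ratio instead of seconds. No change to data collection or sample size is needed.
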